#### Measures for sample size estimation

Clinical outcomes measures. In line with DSM V criteria for AN and OSFED-AN type (atypical AN) which emphasises rate of weight loss and ED cognitions, the primary outcome measure is of eating disorder cognitions and behaviours for sample size estimation—Eating Disorder Examination Questionnaire (EDEQ).^25^ Other indications of symptoms, such as BMI (kg/m^2^); Depression, Anxiety and Stress Scales 21^26^ and Clinical Impairment Assessment^27^ are also collected.

Intervention-specific measures. Other clinical and Intervention-specific measures will also be assessed as follows: Beliefs About Emotions Questionnaire,^28^ Young’s Schema Questionnaire–Short Form (SF),^29^ Schema Mode Inventory ED–SF (SMI-ED-SF)^30^; Silencing the Self Scale,^31^ The Sense of Agency Scale^32^ and Difficulties with Emotion Regulation Scale.^33^

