### Sample size

The feasibility design must balance precision with unethical exposure of participants to the risks being monitored alongside unnecessary expense.^38^ Teare *et al*^39^ recommend 35 participants for sufficient feasibility data and precision of mean and variance. Therapy attrition rates for people with AN can reach 40%.^9^ With a sample size of 36, we will be able to estimate a drop-out rate of 40% to within a 95% CI of ±16%. These data suggest an approximate revised sample size of up to 60 participants in order to achieve a sample of 36 participants completing therapy.

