### Data analysis

The data will be analysed using password protected NHS computers at NELFT. It will be analysed by PIs, the research worker and clinical psychology trainees as part of their doctoral theses. Thematic analysis of acceptability interviews will be completed before quantitative analysis of acceptability data to avoid bias. Dependent t-tests (or non-parametric equivalents) and effect sizes (Cohen’s d) will be calculated for all outcomes measures. EDEQ change will be used in a power analysis to estimate sample size required for effectiveness trial. We will model for missing data of anybody who completed therapy.

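### Missing-data modelling is limited to therapy completers, so the EDEQ change that sizes the later trial is likely, though not certain, to be overstated

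*Protocol article*

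**What the plan says.** The Data analysis section of the protocol article fixes three things.

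- The test: "Dependent t-tests (or non-parametric equivalents) and effect sizes (Cohen’s d) will be calculated for all outcomes measures".
- The use of the result: "EDEQ change will be used in a power analysis to estimate sample size required for effectiveness trial".
- The missing-data rule: "We will model for missing data of anybody who completed therapy".

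Under Measures for sample size estimation, the EDEQ is given its role: "the primary outcome measure is of eating disorder cognitions and behaviours for sample size estimation".

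The Sample size section says "Therapy attrition rates for people with AN can reach 40" per cent, and therefore recruits "up to 60 participants in order to achieve a sample of 36 participants completing therapy".

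The Participant timeline schedules the questionnaires before therapy, at 3, 6 and 9 months, and at 12 months. For people whose therapy was interrupted by the pandemic, a 15-month assessment stands in for the 12-month one.

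The sections on the SPEAKS intervention, on treatment fidelity and on adverse events provide that people who need immediate inpatient treatment, or are admitted to hospital, leave the trial itself and not only the therapy. Nothing in the article provides for the missing outcomes of people who do not complete therapy.

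**The concern.** Completing therapy happens after baseline and may well be related to outcome. Making it the condition for missing-data handling means that the estimate of change comes mainly from people who stayed. The 3-, 6- and 9-month scores of those who left are due to be collected while they are in therapy, but they have no stated part in the pre-post result.

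What is at stake is one of the study's listed objectives: parameters for a future efficacy or effectiveness trial. If that trial is analysed by intention to treat, its participants will include people who stop therapy. A change estimated largely in completers would then describe a different population. If completers improve more than those who leave, the later trial would be planned on too large an effect and would be too small.

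**Working it through.** **1. The plan's own figures.** Inputs from the Sample size section: 36 completers and 40% attrition.

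- Recruitment: 36 / (1 − 0.40) = 60. This reproduces.
- Precision of a 40% drop-out rate at n = 36: 1.96 × √(0.40 × 0.60 / 36) = 0.160. The stated ±16 percentage points reproduce.
- Expected non-completers: 60 − 36 = 24, which is 24 / 60 = 40% of starters.

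The plan's figures are therefore consistent, and they put up to 24 of 60 people outside the missing-data model.

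**2. What the rule does to each group.**

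| Participant | Post-treatment EDEQ | Under the stated rule |
|---|---|---|
| Completer | observed | paired, analysed |
| Completer | missing | modelled |
| Non-completer | observed | not addressed; could be paired |
| Non-completer | missing | no pair and no modelled value, so not in the pre-post test |

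The count of 24 is the upper limit for the last row. It is reached if attrition is 40% and no non-completer supplies a post-treatment score. The article does not say whether post-treatment scores are sought from people who stop therapy but stay in the study. Those withdrawn because of admission have left the study.

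**3. How far the estimate could move.** The article gives no EDEQ change or standard deviation for completers or drop-outs, so this step is an illustration. Let C be the mean change in completers, and let drop-outs change by f × C on average. Assume that none of the 40% contributes a pair. Then:

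- all-starter change = 0.6C + 0.4fC
- ratio of completer change to all-starter change = 1 / (0.6 + 0.4f)

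C cancels, so only f and the attrition rate matter.

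| f (assumed) | 0.6 + 0.4f | Ratio |
|---|---|---|
| 0 | 0.60 | 1.67 |
| 0.5 | 0.80 | 1.25 |
| 1.0 | 1.00 | 1.00 |
| 1.25 | 1.10 | 0.91 |

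For a general attrition share q the ratio is 1 / (1 − q + qf). A smaller q, or some non-completers with observed post-treatment scores, brings it nearer to 1.

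**4. Direction.** Values of f below 1 are the more plausible ones, because one stated route out of the study is a need for admission, which probably goes with a poor outcome. Other routes, such as a request to leave for any reason, say nothing about outcome.

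**The case against.** **The rule does not say that non-completers are excluded.** A reader might infer that all 24 leave the outcome analysis. The text does not support this: it says whose missing values are modelled, defines no analysis set, and does not discard observed data. This objection stands. Loss is certain only for non-completers without a post-treatment EDEQ.

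**Upward bias is not shown.** A reader might also conclude that the EDEQ change is biased upward as a matter of fact. The documents give no outcomes for drop-outs. The bias is nil if they change as much as completers and reverses if they change more. This also stands: the direction is likely, not established.

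**No sample sizes follow.** It is tempting to turn the ratios into numbers per arm for the later trial. That would put a single-arm pre-post change into a two-arm formula. It would need the comparator's change, the standard deviation, alpha and power, none of which the article gives. Mixing two groups with different means also changes the standard deviation. No such figures can be derived here.

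**Drop-out is not ignored, and this is a feasibility study.** The plan estimates the drop-out rate, reports removals, counts people who end therapy because they find it unacceptable, and reports completeness of measures at each time point. It has no efficacy hypothesis. A later team could use these figures to dilute a completer effect. This softens the problem without removing it, because the plan sends the EDEQ change to the power analysis with no such adjustment.

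**The matter might belong in an analysis plan.** A missing rule could be left to one. Here the article states a rule, and the rule is what needs changing.

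**Conclusion.** The point holds in a limited form. The stated rule leaves non-completers without a post-treatment EDEQ out of the pre-post tests, the effect sizes and the change used to plan the next trial. By the plan's own figures this is up to 24 of 60 starters.

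Overstatement of the change is the likely result. Over the assumed range its size runs from a ratio of 1.67 (drop-outs do not change) through 1.00 (they change equally) to 0.91 (they change by a quarter more). These ratios rest on 40% attrition, on no non-completer contributing a pair, and on assumed values of f. Because 40% is given as a rate that attrition can reach, the 24 and the ratios furthest from 1 are upper-end figures.

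**What to change.** Replace the missing-data sentence with text to this effect: all participants who start SPEAKS are included in the outcome analysis. EDEQ scores from every scheduled assessment (baseline, 3, 6, 9 and 12 months, or 15 months where therapy was extended) are analysed with a likelihood-based mixed model or multiple imputation, using scores obtained before drop-out. The power analysis for the later trial uses the change estimated this way.

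Both methods assume that data are missing at random, which may fail if people leave because they are doing badly. Two kinds of sensitivity analysis should therefore be added: a completer-only analysis, which keeps the estimate now planned, and missing-not-at-random scenarios, for example no change from baseline for non-completers.

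No new visits are needed, since the three-monthly scores are already scheduled. The cost is slightly more analysis work and, probably, a smaller reported change.

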## Methods: monitoring

### Data monitoring

A Research Steering Committee (RSG) composed of the research team including CI and PIs, representatives from the sponsors, representatives from both EDS and PPI members (with history of anorexia and family members) oversees the SPEAKS research programme. It is chaired by an experienced researcher independent from trial Trusts and sponsor. The RSG meets every 6 months for reporting and discussion. Additional meetings can be convened at short notice if required. The RSG chair is available for independent advice to the research team.

### Patient and public involvement

PPI has been in place since the inception of the study before trial funding was sought. An initial Research Design Service PPI Grant covered costs of a consultation series to assess SPEAKS model and trial validity. This informed intervention development, study design and the SPEAKS name. Following trial funding, feedback on key documents such as the plain English summary and participant information sheets (PIS) were obtained via contacts made in this initial consultation. Further, PPI input continues throughout the study via the RSG and in open feedback events at key stages of the study advertised via local charity and support group networks.

### Adverse event reporting and harms

Protocol violations such as hospital admission are recorded as per Trust guidance, and logged in trial records for reporting. Participants admitted to hospital will be withdrawn from the study. All research staff are NIHR Good Clinical Practice (GCP) trained and follow these guidelines for safety reporting procedures. Due to the feasibility design, there are no interim analyses or stopping guidelines; however, therapists monitor participant safety with regular risk assessments and communicate to the research team. Events leading to participants or others experiencing potential or actual serious harm are recorded by the researcher and reported to the PI and sponsor within 24 hours of knowledge of the event. Decision on expectedness and relatedness to the study intervention will be taken, with further investigation as required. The PI and sponsor will monitor events in case a pattern emerges, taking action if necessary. Clinical risk will be managed within ED service guidelines. Following completion of trial participation, all usual clinical service and NHS Trust SOP continue to apply with post-trial care continuing if clinically indicated. During the trial all usual Trust complaint procedures can be followed.

### Auditing

Overall study conduct, and conduct at individual sites, will be monitored by the Sponsor Monitor at regular intervals. The Trial Master File (TMF) will be audited at site initiation, annually for the duration of the study and at study closure. This audit will follow the sponsor SOP and includes checks of: completeness and secure storage of TMF, study-wide approvals, study-wide safety and deviation/violation reporting, GCP compliance and performance of study against recruitment targets.

Individual research sites will be monitored after five participants have been recruited as part of site initiation, annually from site initiation date and at study closure at site. Monitoring will follow the sponsor SOP and include monitoring of the investigator site file for completeness and secure storage, SDV checks, CRF checks, serious adverse events and deviation/violation checks, GCP compliance and performance of site against recruitment targets.

### Ethics and dissemination

#### Research ethics approval

This study has been reviewed in accordance with the guidelines for Canterbury Christ Church University research and has been approved by the London–Bromley Research Ethics Committee (NHS Rec Reference REC Ref: 19/LO/1530).

#### Protocol amendments

Any protocol amendments will be communicated to all relevant parties and research sites. Notice of intention to submit an amendment will be provided via email to the sponsor and the research governance representatives at all sites to offer an opportunity to discuss any queries prior to submission and confirm support. Ethical approval will subsequently be sought via online submission following IRAS guidance. Once ethical approval has been granted for an amendment this will be disseminated to all parties and official registries (such as ISRCTN) will be notified.

#### Consent

Patients meeting inclusion criteria will be provided with a PIS by their assessing clinician if they are willing to hear more about the study. Informed consent will be obtained at a face-to-face meeting with a member of the research team. The meeting will take place at least 48 hours after the participant has been provided with the PIS, with additional time given as necessary.

At the consent appointment, the research worker will answer any initial questions from the potential participant. They will review the PIS, highlighting key aspects and checking the patient’s understanding of what study involvement entails. The researcher will explicitly state and make clear that deciding not to participate will not affect the patient’s care in any way, and that if they decide to take part they can change their mind at any time without affecting their current or future care. The research team (like all other clinical staff members) will be trained in the principles of mental capacity and will hold this in mind throughout. Obtaining consent will be a focus of research supervision.

#### Confidentiality

In line with usual clinical practice, all participant information will be kept confidential, except as governed by law (ie, if there is a legal obligation on the researcher to disclose this information to authorities due to risk concerns).

Signed informed consent forms will be stored separately from completed questionnaires and interview transcripts, which will be notated with only a participant number and/or pseudonym. Signed informed consent forms will be kept in a locked cabinet on NELFT or SPFT Property as relevant. Completed questionnaire data will be entered into study databases in encrypted Trust network folders accessible only to the research team. Any video recordings of therapy sessions and formulation descriptions will be stored on secure encrypted password protected NHS hard drives.

Participant identity will not be included in written interview transcripts, and will not be revealed in any publication resulting from this study. Data gathered from this study will be retained as required by regulations, which is up to 10 years following publication of empirical articles or communications describing study results.

### Availability of data and materials

Study databases and TMFs will only be available to the research team employed by the participating Trusts. The trainee psychologists analysing video recordings and psychological formulation data will not know participant identity beyond what they see in recorded therapy sessions. Qualitative interview recordings may be transcribed by a third-party agency approved by the sponsor. Participant names and personal details will not be disclosed and full confidentiality agreements will be established as per this protocol.

#### Dissemination policy

Data will be disseminated via high-impact, peer-reviewed journals, with Open Access sought where possible. Papers will be submitted for conference presentations to achieve dissemination to practitioners and professionals within the ED field. Dissemination to service users and clinical networks is considered extremely important and be achieved via service user networks across NHS Trusts and Higher Education Institutions (HEIs) involved in the study, via charity networks (eg, UK eating disorder charity BEAT) and through a free open conference hosted by the NHS Trusts and HEI to disseminate findings and facilitate feedback on the SPEAKS clinical model and intervention. The decisions of when and where to publish data and authorship eligibility is decided by the SPEAKS RSG. Professional writers will not be used.

## Discussion

This SPEAKS feasibility trial aims to assess acceptability, research and recruitment, sample size estimation and initial economic indications of the SPEAKS intervention for adults with AN Otherwise Specified Feeding or Eating Disorder-AN type. It also tests the hypothesised change process of the SPEAKS intervention.

### Potential implications

This first test of the SPEAKS intervention will provide initial indication of the feasibility of SPEAKS and inform whether progression to larger trials is appropriate. Change process analyses will provide valuable insights into SPEAKS hypotheses, informing refinement of the intervention, while also contributing to broader evidence-base of relevant change processes for adults with AN.

### Strengths

This feasibility trial is strengthened by multi-site design. Furthermore, sites included are relatively research naïve in delivery of clinical trials facilitating realistic insights into the feasibility of intervention delivery within naturalistic NHS services. Inclusion of consecutive referrals enables broad spectrum of participants across AN and OSFED severity and presentations, increasing generalisability. Robust measures to facilitate adherence to the model are included.

### Challenges

SPEAKS is an experiential, relational model, designed for face-to-face settings. This trial began in the wake of the COVID-19 pandemic resulting in therapy sessions moving indefinitely to online video platforms with most participants never meeting their therapist in person. People with AN are often regarded as ‘difficult to engage’ and have high levels of therapy dropout, thus issues of engagement with clinical and research protocols are a challenge even without this context. These factors may affect outcomes or length of delivery.
